# Wrist-ankle acupuncture (WAA) for precompetition nervous syndrome: study protocol for a randomized controlled trial

**DOI:** 10.1186/s13063-015-0910-z

**Published:** 2015-09-07

**Keywords:** Wrist-ankle acupuncture (WAA), Precompetition nervous syndrome, Anxiety, Randomized controlled trial

## Abstract

**Background:**

Precompetition nervous syndrome comprises an excessive nervous and anxiety response to the high-pressure environment preceding a sporting competition. The use of acupuncture as a treatment option for anxiety, and wrist-ankle acupuncture (WAA) specifically in this instance, has been identified as a growing trend within the Western world. In our previous study, we have confirmed the efficacy of WAA for pre-examination anxiety. In this paper, we present a randomized controlled single-blind trial evaluating the use of WAA for precompetition nervous syndrome, comparing it with the intervention of sham acupuncture.

**Methods/Design:**

The study was designed as a randomized controlled single-blind trial to evaluate the effects of WAA for precompetition anxiety. The trial will be conducted in annual track and field events of Shanghai University of Sport. A total of 100 participants who meet inclusion criteria are randomly assigned by computerized randomization to receive WAA therapy or sham acupuncture. The group allocations and interventions are concealed to participants and statisticians. The Competition State Anxiety Scale (CSAI-2) is used as the primary outcome measure, while heart rate, blood pressure, respiratory frequency, tension syndrome curative effect evaluation and participants’ feeling of acupuncture questionnaire are applied as secondary outcome measures.

**Discussion:**

The results of this trial will confirm whether WAA is effective to treat precompetition anxiety in annual track and field events.

**Trial registration:**

Chinese Clinical Trial Registry (identifier: ChiCTR-TRC-13003931; registration date: 22 October 2013).

## Background

With unceasing improvement in the standard of modern sports at competitive level, the gap between the level of athletic technique and physical ability is ever diminishing. The results of the competition often depend not only on the gap between technique and physical ability, but are greatly influenced by the athletes’ psychological fitness. Thus, psychological factors have become an important component of performance in modern competitive sports.

Precompetition nervous syndrome comprises an excessive nervous and anxiety response to the high-pressure environment preceding a sporting competition. Although a certain level of anxiety enhances performance, uncontrolled emotions and negative cognitions can have adverse effects [1–3]. Various techniques have been used to help athletes control their emotions. These include self-breathing training, biofeedback training, meditation, visuomotor behavior rehearsal, hypnosis, and cognitive behavioral therapies [4]. The clinical trial evidence supporting the lasting effectiveness of these methods for athletes is limited and generally weak [5]. It is apparent that research is greatly needed in this area. Moreover, it is apparent that a robust intervention to consistently control performance anxiety is also critically needed.

Acupuncture has been used worldwide for various types of disorders of spirit and emotion, such as depression, anxiety and insomnia [4–10]. In some international sporting events, like the 2010 Asian Games of Guangzhou, a South Korean player received acupuncture when competing with her rival at the game of *Go* in order to help her to keep relaxed and calm. This suggests that using acupuncture in sports is feasible for players’ mental preparation. On the other hand, traditional acupuncture treatments emphasize the “needling sensation”, which will give an unpleasant feeling to some players. Knowledge of these effects has impeded the wider acceptance of traditional acupuncture treatments in the games. Wrist-ankle acupuncture (WAA) is a modern acupuncture technique invented and developed by [name] and his colleagues from Changhai Hospital of Second Military Medical University, Shanghai, China in the 1970s [11]. The theory of WAA has a unique system of its own, which is quite different from that of traditional acupuncture [12]. WAA does not produce the “needling sensation” and has demonstrated good effects for mental and nervous disorders. More importantly, the lack of pain and “needling sensation” during the performance of WAA imposes minimal psychological stress on the player and hence is readily accepted.

Previously, we have confirmed the efficacy of WAA for pre-examination anxiety [13]. In the study we observed that WAA can significantly alleviate exam tension and that the treatment is very safe. However, to date, there are no studies investigating the application of WAA for managing precompetition anxiety in athletes. The present study attempts to investigate the effects of WAA for athletes with precompetition anxiety in annual track and field events.

The trial protocol here is in accordance with Consolidated Standards of Reporting Trials (CONSORT) 2010 statement [14]. The intervention WAA details are described in accordance with the STandards for Reporting Interventions in Clinical Trials of Acupuncture (STRICTA) 2010 extension [15].

## Methods/Design

### Ethics review and informed consent

The study protocol was reviewed and approved by the Chinese Ethics Committee of Registering Clinical Trials (ChiECRCT-2013024), and subsequently in the Chinese Clinical Trial Registry (ChiCTR-TRC-13003931). All participants are required to provide informed consent.

### Study design

The study was designed as a randomized controlled single-blind trial to evaluate the effects of WAA for precompetition anxiety (Fig. 1). The trial will be conducted in annual track and field events of Shanghai University of Sport.

**Fig. 1 Fig1:**
[figure not shown]
Flowchart of the study design

### Study procedure and patient recruitment

The trial information leaflets will be distributed to the university campus to recruit potential participants 1 week before the competition. The leaflets contain a brief questionnaire for screening participants with precompetition nervous syndrome. Those who have two or more major symptoms of excessive nervous and anxious, insomnia, fear of failure, and inattention are recruitable. One item in the questionnaire is to distinguish whether these symptoms are responses that are present before the competition [16]. Participants are included only if they meet the inclusion criteria and sign an informed consent document. The protocol details are also explained to the participants in the leaflets and all the basic information will be provided to the researcher.

### Key inclusion and exclusion criteria

#### Inclusion criteria

Sport university students, age 18 to 40 years old, both male and female participants;The patient must not yet have previously received the WAA treatment;The patient must have signed the informed consent.

#### Exclusion criteria

Precompetition nervous syndrome participants using drugs or other concurrent systems;A history of mental illness or physical disease;A depressive trend (depression self-rating scale score ≧ 41).

### Data collection

All the participants will be asked to complete two identical scale questionnaires and physical condition examinations before and after the treatment in order to assess their anxiety levels. The first questionnaire and physical condition examination must be completed 30 minutes before the treatment, while the second one will be collected 30 minutes after the treatment.

### Treatment regimen

Participants are required to receive 1 treatment 3 hours before the track event sessions to minimize uncertainty in the selection of different events (only track event athletes are included as subjects).

### Interventions

The treatment scheme originates from the principles of WAA and has been practiced in previous clinical trials for several decades [11–13, 17–20]. According to the theory of WAA, each side of the body and each limb are longitudinally divided into six zones and one needling point is defined in each zone at the wrist or ankle. Needling point 1 on the wrist zone (point upper 1) can relieve disorders of emotion. For participants in the current study, precompetition anxiety belongs to disorders of emotion; therefore, all subjects were needled at point 1 at both wrists (Fig. 2).

**Fig. 2 Fig2:**
[figure not shown]
Wrist-ankle acupuncture (WAA) needling point 1 on the wrist zone (point upper 1) after insertion. Point upper 1 is located on the pit between the medial border of the ulnar and the tendon of musculus flexor carpi ulnaris

WAA group: WAA was administered on point upper 1 at both wrists, 3 hours before the track event sessions. The needle was retained for 30 minutes. The subjects were asked to stay in the sitting position and to wear an eye mask. The target point was disinfected with an iodophor disinfectant (Shanghai Likang Disinfectant Hi-tech Co. Ltd., Shanghai, China). The processed needles were also held with three right-hand fingers (thumb, index finger, and middle finger). The skin near the target point was gently pressed with the left thumb to make it slightly taut. A disposable sterile WAA needle (0.25 mm in diameter and 25 mm in length, Suzhou Medical Appliance Factory, Jiangsu Province, China) was held with three right-hand fingers (thumb, index finger, and middle finger). Then, the needle tip was swiftly inserted into the skin at the target point at a 30° angle. The needle was lowered to the horizontal position and slowly advanced until the entire needle (except the handle) entered the subcutaneous tissue. The handle was then fixed to the skin with an adhesive tape. The needles were retained in the subcutaneous tissue for 30 minutes. For a successful WAA treatment, the patient will only feel a negligible stabbing pain when the tip of the needle pierces the skin. No other needling sensation will be experienced. A single registered acupuncturist, with at least 1 year of previous WAA experience, administered the care to all subjects [11, 17].

Sham acupuncture group: sham acupuncture was administered on point 1 at the wrists, 3 hours before the track event sessions. The needle was retained for 30 minutes. The subjects were asked to stay in the sitting position and to wear an eye mask. The target site was also disinfected with an iodophor disinfectant (Shanghai Likang Disinfectant Hi-tech Co. Ltd., Shanghai, China). The tip and most of the body of the disposable sterile acupuncture needle (0.25 mm in diameter and 25 mm in length, Suzhou Medical Appliance Factory, Jiangsu Province, China) (Fig. 3) was cut off and blunted. Only 2–3 mm of the length of the needle body remained. The processed needles were also held with three right-hand fingers (thumb, index finger, and middle finger). The skin near the target site was gently pressed with the left thumb to make it slightly taut. The needle tip swiftly punctured the skin at the target point at a30° angle (the tip was not actually inserted into the skin). Then, the needles remained horizontally on the skin of the point for 30 minutes. The handle was also fixed to the skin with adhesive tape. For a successful sham treatment, the patient will also only feel a negligible stabbing pain when the tip of the needle pierces the skin. No other needling sensation will be experienced. As with the WAA group, a single registered acupuncturist with at least 1 year of previous WAA experience, administered the care to all subjects.

**Fig. 3 Fig3:**
[figure not shown]
Wrist-ankle acupuncture (WAA) needle and sham acupuncture needle. The WAA needle is a disposable sterile needle (0.25 mm in diameter and 25 mm in length, Suzhou Medical Appliance Factory, Jiangsu Province, China); the sham acupuncture also uses the same model needle (0.25 mm in diameter and 25 mm in length, Suzhou Medical Appliance Factory, Jiangsu Province, China), although the tip and most of the body was cut off and blunted. Only a 2–3 mm length of the needle body remained

### Randomization and blinding

An outside researcher who is not allowed to directly contact with the participants will perform computerized randomization. The assessor will also be blinded to the treatment allocation. The acupuncturist performing the WAA intervention and sham WAA intervention cannot be completely blinded, but he is not be allowed to reveal any information about treatment procedures and outcomes to the participants or the assessor. Thus, both the participants and the assessor will not distinguish clearly which intervention has been given. A sealed envelope containing an allocation sequence number for each participant will be opened after each participant meets eligibility criteria and informed consent is obtained. If any error or disclosure with regard to randomization occurs, a new randomization sequence will be generated, starting from the problematic serial number, and subsequently applied to the participant.

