### Sample size calculation and statistical analysis

The sample size is estimated, based on changes of Competition State Anxiety Scale (CSAI-2) before and after treatment, from a pilot study. The pilot study was a two-arm design with WAA group and sham acupuncture group. The means of changes of WAA group and sham acupuncture group are 1.9 and −2.0 respectively, while the standard deviations are 6.9 and 5.5. The software Power Analysis and Sample Size (SAS version 9.3, SAS Institute Inc., Cary, NC, USA) was used to perform the sample size calculation. The sample size was calculated with a significance level of 0.05 and power of 0.80. The result was a total required sample size of 86, with 43 for each group. With a maximum dropout tolerance of 15 %, 7 participants are needed for each group. Therefore, 100 participants are needed for the trial, with 50 for each group.

Statistical analysis will be performed using SPSS 15.0 statistics software (SPSS Inc., Chicago, IL, USA) and the statistician is blinded from group allocation. For quantitative data, the distribution pattern and homogeneity of variance will be examined. If there is a symmetric distribution, the mean (M) ± standard deviation will be used for statistical description. A paired samples *t* test will be examined to compare the differences between the quantitative indices before and after treatment in one group, while an independent sample *t* test will be used for comparison between groups. The entire statistical test will use bilateral examination where *P* < 0.05 indicates statistically significant difference.

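### The rule for randomization errors or disclosures is not limited to unopened allocations, so an enrolled participant's known allocation can be replaced by a second draw

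*Protocol article*

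**What the plan says.** All the relevant text stands in one paragraph of the protocol article, under Randomization and blinding.

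- Generation: "An outside researcher who is not allowed to directly contact with the participants will perform computerized randomization".
- Opening: each participant's sealed envelope "will be opened after each participant meets eligibility criteria and informed consent is obtained".
- Knowledge of the arm on site: "The acupuncturist performing the WAA intervention and sham WAA intervention cannot be completely blinded". The acupuncturist is barred from passing information to participants or to the assessor.
- Contingency rule: "If any error or disclosure with regard to randomization occurs", then "a new randomization sequence will be generated, starting from the problematic serial number, and subsequently applied to the participant".

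The contingency rule is a positive instruction, not a gap that a fuller document might fill. It covers any error or disclosure and sets no condition on whether the envelope is still sealed.

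**The concern.** A sequence that starts from the problematic number includes that number, and the rule says that the new draw goes to the participant. If the envelope has been opened, that person is already eligible, consented and assigned, and the arm is known to someone. The rule then replaces a known allocation with a second random one.

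Two things are at stake. First, concealment protects the comparison only if nobody can act on an allocation after seeing it. Here, a report of an error or disclosure, made by someone who has seen the arm, can lead to another draw. Second, an analysis by assigned group needs one assignment per participant. The rule displaces the first assignment for exactly those whose handling was irregular.

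**Working it through.** **1. The plan's own figures.** The article gives no figure for this rule. Its one design calculation, under Sample size calculation and statistical analysis, reproduces closely. The inputs are "The means of changes of WAA group and sham acupuncture group are 1.9 and −2.0 respectively", a difference of 1.9 − (−2.0) = 3.9, and standard deviations 6.9 and 5.5, so the root mean square is √((6.9² + 5.5²)/2) = 6.24. "The sample size was calculated with a significance level of 0.05 and power of 0.80", and "The entire statistical test will use bilateral examination". The two-sample t test then needs 42 per group (power 0.808), against the stated 43 (power 0.817). The point below does not change this calculation.

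**2. The clauses in time order.** Consent comes first, then opening of the envelope, then treatment. The trigger can fall on either side of the opening:

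- Before opening: the participant has no known allocation. A fresh draw for that number and later ones restores concealment. This is sound.
- After opening: the participant has a known allocation. A fresh draw replaces it. This is the defect.

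The rule does not separate the two cases.

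**3. Chance of the preferred arm.** Assume 1:1 allocation (the plan has 50 per group), a fresh 1:1 re-draw, and at most one re-draw per participant. Let q be the probability that the rule is invoked when the unwanted arm is seen, and assume it is never invoked when the preferred arm is seen. Then

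P(preferred) = 0.5 + 0.5 × q × 0.5 = 0.5 + 0.25q.

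| q | P(preferred) |
|---|---|
| 0.05 | 0.5125 |
| 0.1 | 0.525 |
| 0.2 | 0.55 |
| 0.5 | 0.625 |
| 1 | 0.75 |

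These are probabilities before the first draw. Once an unwanted arm has been seen and a re-draw granted, the chance of the preferred arm is 0.5. If every participant were exposed to the same q, the expected number of re-draws among 100 would be 100 × 0.5 × q = 50q: 5 at q = 0.1, of which half would change arm. One participant is 1/50 = 2% of an arm.

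If the rule is invoked with probability r whichever arm was drawn, P(preferred) = (1 − r) × 0.5 + r × 0.5 = 0.5, so nothing is lost.

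**4. From allocation to bias.** A q that is the same for everyone only shifts the allocation ratio. Bias in the effect needs the trigger to depend on the participant as well. As an illustration, suppose that half the participants (type A) are steered towards WAA and half (type B) towards sham, with the same q. Type A then makes up 0.5 + 0.25q of the WAA group and 0.5 − 0.25q of the sham group, a gap of 0.5q. If the types differ in change score by G for reasons other than treatment, the bias is 0.5q × G. With G assumed to be one standard deviation, 6.24:

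- q = 0.1: 0.05 × 6.24 = 0.31 points, 8% of the planned difference of 3.9.
- q = 0.2: 0.10 × 6.24 = 0.62 points, 16%.
- q = 1: 0.50 × 6.24 = 3.12 points, 80%.

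Neither q nor G is in the article. These values show scale only.

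**The case against.** The strongest defence is that the rule may be meant for faults found before an envelope is opened, such as a leaked list, a damaged envelope or a numbering error. Regenerating from the compromised number is then correct practice. The draw also stays with an outside researcher who has no direct contact with participants, and the clause may never be used.

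Much of this stands. The rule does cover sound cases, and the outside researcher lowers the risk. Two parts do not answer the point. The wording is not confined to unopened envelopes. And an independent draw does not guard against a selective request to draw again: a person without participant contact would normally learn of an error or disclosure from others.

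A reader might also infer more than the article supports:

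- That the unblinded acupuncturist triggers re-draws. The article says only that he cannot be completely blinded. It does not say who opens envelopes or declares an error.
- That the audit trail is destroyed. A new sequence is generated, but nothing says that the old list is discarded or the event left unrecorded.
- That treated participants are relabelled. Treatment is a single session, and the text describes no re-allocation after needling.
- That a stated intention-to-treat analysis is contradicted. The article names no such population. The difficulty comes from the displaced assignment itself.

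**Conclusion.** The point holds in a limited form. As written, the rule permits a known allocation of an enrolled participant to be replaced by a second draw, which opens a route to selection bias and displaces the first assignment. It would be going too far to say that the rule breaks concealment in every use, or that the trial is biased: there is no evidence that it was used, or used selectively.

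Under a single 1:1 re-draw, the chance of a preferred arm rises from 0.5 to 0.525 or 0.55 at 10% or 20% selective use. The figure of 0.75 is a ceiling that requires the rule to be invoked every time the unwanted arm appears. A trigger unrelated to the arm adds no bias. Sample size and the planned tests are unaffected. The weakness is worth correcting because it lies in a stated instruction and the remedy is simple.

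**What to change.** Limit the rule by whether the envelope has been opened:

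- Unopened: the outside researcher may regenerate the sequence for those serial numbers only.
- Opened: the allocation is final. The participant is analysed in the first assigned group, and the error or disclosure is logged as a deviation.

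The article's Trial status section says recruitment is under way, with completion due on 30 September 2015, so part of the remedy is retrospective. Report how often the rule was used and whether each use came before or after opening. Analyse any participant already re-drawn by first assignment, and add a sensitivity analysis that excludes them.

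The cost is a short change to the protocol text, a log and one further analysis if anyone was re-drawn. No extra participants are needed.

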### Sample size calculation and statistical analysis

The sample size is estimated, based on changes of Competition State Anxiety Scale (CSAI-2) before and after treatment, from a pilot study. The pilot study was a two-arm design with WAA group and sham acupuncture group. The means of changes of WAA group and sham acupuncture group are 1.9 and −2.0 respectively, while the standard deviations are 6.9 and 5.5. The software Power Analysis and Sample Size (SAS version 9.3, SAS Institute Inc., Cary, NC, USA) was used to perform the sample size calculation. The sample size was calculated with a significance level of 0.05 and power of 0.80. The result was a total required sample size of 86, with 43 for each group. With a maximum dropout tolerance of 15 %, 7 participants are needed for each group. Therefore, 100 participants are needed for the trial, with 50 for each group.

Statistical analysis will be performed using SPSS 15.0 statistics software (SPSS Inc., Chicago, IL, USA) and the statistician is blinded from group allocation. For quantitative data, the distribution pattern and homogeneity of variance will be examined. If there is a symmetric distribution, the mean (M) ± standard deviation will be used for statistical description. A paired samples *t* test will be examined to compare the differences between the quantitative indices before and after treatment in one group, while an independent sample *t* test will be used for comparison between groups. The entire statistical test will use bilateral examination where *P* < 0.05 indicates statistically significant difference.

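### Within-arm before-after t tests share the P < 0.05 rule with the between-arm test, and the plan does not say which one decides efficacy

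*Protocol article*

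**What the plan says.** All of this stands in the protocol article, under Sample size calculation and statistical analysis. One sentence plans two kinds of test for quantitative data. The first is within each arm: "A paired samples *t* test will be examined to compare the differences between the quantitative indices before and after treatment in one group". The second is between arms: "while an independent sample *t* test will be used for comparison between groups". The next sentence covers both: "The entire statistical test will use bilateral examination where *P* < 0.05 indicates statistically significant difference".

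Description is dealt with separately, by mean and standard deviation, so the paired tests are inferential as written. The section on the primary outcome says that CSAI-2 serves to judge the efficacy of treatment but does not name the test that does so.

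The sample size rests on the contrast between arms in a pilot study: "The means of changes of WAA group and sham acupuncture group are 1.9 and −2.0 respectively", "while the standard deviations are 6.9 and 5.5". The stated result is: "The result was a total required sample size of 86, with 43 for each group".

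**The concern.** The sham arm is there to remove everything that both arms share. The sections on data collection, treatment regimen and interventions show how much that is. Participants are assessed 30 minutes before and 30 minutes after a treatment given 3 hours before the race. They sit with an eye mask for 30 minutes while the needles are in place, and they fill in the same questionnaire twice. Over that interval the CSAI-2 score can move in either direction for reasons unrelated to the needle. A paired test within one arm asks whether the score moved, not whether WAA moved it more than sham did.

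Two misuses are left open. A significant before-after change under WAA could be reported as efficacy. Or the two arms' P values could be set side by side, and significance in WAA but not in sham read as a difference between them. That comparison does not test a difference, and its error rate depends on the size of the shared change. The Discussion expects high-quality evidence on efficacy from the sham-controlled design, and a within-arm P value cannot supply it.

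**Working it through.** **Inputs from the article.** Pilot mean changes +1.9 (WAA) and −2.0 (sham), difference 3.9; SDs 6.9 and 5.5; two-sided alpha 0.05; power 0.80; 43 evaluable per arm, 50 recruited. I take the SDs to be SDs of change, as the text implies, and the changes to be roughly normal.

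**Step 1. Reproduce the stated sample size.**
- Pooled SD = √((6.9² + 5.5²)/2) = 6.24.
- Normal approximation: n = 2 × 6.24² × (1.960 + 0.842)² / 3.9² = 40.2, so 41 per arm.
- The noncentral t needs 42 per arm (power 80.8%). At the stated 43 the power is 81.7%, and at 50 it is 87.1%.

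The stated 43 per arm therefore reproduces to within two. The calculation is a between-arm calculation.

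**Step 2. Chance that one paired test is significant when there is no treatment effect.** Assume that both arms truly change by the same amount m, with SD 6.24 and n = 43. The noncentrality is m / (6.24/√43) = m / 0.951, with 42 degrees of freedom. Call the two-sided significance probability p. The article gives no figure for a shared change, so m is an assumption and a range is shown. The value of 2 points is the absolute size of the pilot change under sham.

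**Step 3. Chance that the two arms disagree.** The arms are independent, so P(exactly one significant) = 2p(1 − p) and P(WAA only) = p(1 − p).

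| Common change m | p per arm | Exactly one arm significant | WAA only |
|---|---|---|---|
| 0 | 0.050 | 9.5% | 4.8% |
| 1 | 0.177 | 29% | 15% |
| 2 | 0.537 | 50% | 25% |
| 3 | 0.869 | 23% | 11% |

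Under the same conditions the between-arm test rejects in 5% of trials in total, counting both directions, whatever m is.

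**Step 4. Sensitivity to n.** With 50 per arm and m = 2, p = 0.603 and exactly one arm is significant in 48% of trials. The conclusion does not turn on which n is used.

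**Step 5. The paired tests at the pilot values.** For WAA, t = 1.9/(6.9/√43) = 1.81, P = 0.078, power 42%. For sham, t = −2.0/(5.5/√43) = −2.38, P = 0.022, power 64%. These figures show only that the paired tests answer a different question from the between-arm test. They are not evidence of harm, for the reasons given under the objection.

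**The case against.** The strongest reply is that the right test is already there. The independent-samples t test is planned, the sample size is built on it, and the abstract frames the objective as WAA compared with sham. Nowhere does the article say that efficacy will be judged from a paired test or from significance in one arm only. A condensed article may also leave the order of tests to a fuller plan. Most of this stands. The defect is not a missing comparison, and the rates in the table apply only if someone adopts a rule that the plan does not state. But the article does fix the paired tests as inferential, at the same threshold as the deciding test, and that choice can be criticised on its own text.

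The 50% figure also needs its context. It sits at the maximum of 2p(1 − p). At zero shared change the figure is about 10%, and WAA-only significance, the pattern most likely to be misread as efficacy, is half of each entry.

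Three stronger readings might be inferred and are not supported.
- Step 5 might suggest that the plan favours a finding under sham over one under WAA. The pilot changes have opposite signs, so a significant sham result would lie in the direction opposite to WAA, which agrees with a difference between arms. Neither the sign convention nor the subscale is stated, and a higher score is unfavourable on two of the three subscales and favourable on self-confidence. The article therefore cannot show which arm improved.
- A reader might think that the paired tests could hide a real effect. The between-arm test is still run, with about 82% power at 43 per arm, and no paired P value alters its result.
- Regression to the mean might be added to the shared influences. Screening uses a symptom questionnaire 1 week before the competition, not a CSAI-2 threshold, and the CSAI-2 baseline is taken separately. The point does not rely on it.

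**Conclusion.** The point holds as a minor one. The article plans before-after tests in each arm under the same two-sided 0.05 rule as the between-arm test and does not say which decides efficacy. A within-arm P value cannot support efficacy against sham.

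If the two within-arm results were compared, which the plan leaves open but does not propose, the arms would disagree in about 10% to 50% of trials with no treatment effect, over shared changes of 0 to 3 points. WAA alone would be significant in about 5% to 25%, against a total of 5% for the between-arm test. These rates assume normal changes, a common SD of 6.24, 43 per arm and a shared change that the article does not give. That a within-arm test lacks a control holds without any of these assumptions.

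**What to change.** Amend the statistical analysis section in two places.

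1. Report the mean change within each arm, with its SD or confidence interval, as description only and without P values. This replaces the paired t tests as inferential tests.
2. State that the efficacy conclusion rests solely on the between-arm difference in CSAI-2, adjusted for the pre-treatment score, with its 95% CI. Analysis of covariance would do this. The hierarchy is the core of the change. The baseline adjustment is a further improvement that uses a measurement already collected.

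The cost is negligible: wording in the analysis section, with no new data, assessments or participants. The description of change within arms is kept.
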